#### Power Calculation

Due to the anticipated difficulties in recruitment that will likely arise from the complexities of running a study during a pandemic and the time-sensitive nature of implementing an early sleep intervention relative to both the start of the pandemic and insomnia symptoms, we view this trial as a feasibility study. Therefore, for this feasibility trial, we aimed to recruit a total of 50 subjects, which would result in 25 subjects in each study group. With this sample size, our power calculations were derived using the 2-group *t* test of equal means based on the difference between CBT-I and waitlist control group at 28 weeks, at a 5% level of significance. With 25 per group, the study is 80% powered to detect a large effect size (Cohen d=0.80).

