#### Primary Analyses

Statistical analyses aim 1 is to determine whether a brief, telehealth CBT-I reduces insomnia symptoms arising during the COVID-19 pandemic. All primary analyses will be performed using the intention-to-treat principle. We will test whether CBT-I is superior to a waitlist control in reducing insomnia symptoms by using a mixed effects linear model with autoregressive error structure using intention-to-treat analysis with outcomes at time points 6, 12, and 28. Insomnia severity as measured by the ISI will be entered as the dependent variable with randomization group (2 levels), time point (weeks 0, 6, 12, and 28), and group-by-time interaction included as fixed effects. The model will also include a random slope. Several hypotheses (1.1a-d) will be tested using the described mixed effects model.

Hypothesis 1.1a is that individuals assigned to the CBT-I group will experience an improved trajectory of insomnia symptoms during the waitlist-controlled 28-week period relative to those assigned to the waitlist control group. This hypothesis will be tested using a likelihood ratio test of the coefficients of the time and group-by-time interaction of the aforementioned mixed effects linear model.

Hypotheses 1.1b-1.1d are that individuals assigned to the CBT-I group during the waitlist-controlled period will have lower insomnia symptoms compared with those assigned to the waitlist-control group immediately posttreatment (hypothesis 1.1b; week 6) and at the short-term (hypothesis 1.1c; week 12) and long-term (hypothesis 1.1d; week 28) follow-ups. These hypotheses will be tested using the aforementioned mixed effects linear model with independent likelihood ratio tests using the treatment coefficient for the posttreatment (hypothesis 1.1b; Δ_1_ in Figure 2), short-term (hypothesis 1.1c; Δ_2_ in Figure 2), and long-term (hypothesis 1.1c; Δ_3_ in Figure 2) follow-up time points.

We will also test whether CBT-I is superior to the waitlist control in preventing an insomnia diagnosis following treatment by using multiple logistic regression analysis.

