## Results

### Trial Status and Timeline

The trial began recruitment on June 4, 2020, and the first participant was consented on June 10, 2020. As of October 2021, 794 subjects had completed prescreening, and 96 subjects had completed a Zoom screening session. A total of 49 participants were randomized to a study group (26 to the CBT-I group and 23 to the waitlist control group). Overall, 38 participants had completed the week 6 follow-up, 37 had completed the week 12 follow-up, 34 had completed the week 28 follow-up, and 15 had completed the week 56 follow-up. At the time of this writing, there were an additional 3 participants awaiting the 28-week follow-up and a total of 23 participants awaiting the week 56 follow-up (13 in CBT-I and 10 in waitlist control group). The study closed to enrollment of new subjects on June 17, 2021. As of the writing of this paper, due to the outstanding data collection of the remaining 28- and 56-week data, we had conducted interim analyses for the week 6 follow-up but had not tested the results of our primary hypotheses in full. We expect primary results of the study to be published in 2022.

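### Likelihood ratio tests for hypotheses 1.1a-d and 2.2a-d are mildly liberal at this sample size; REML with small-sample t and F references would be better

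*Protocol article*

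**What the plan says.** Under Primary Analyses, the insomnia outcome (ISI) is modelled by a linear mixed model with autoregressive errors and a random slope. Group, time point (weeks 0, 6, 12 and 28) and their interaction are fixed effects. Hypothesis 1.1a (trajectory) is a likelihood ratio test of the time and interaction coefficients. Hypotheses 1.1b-d (weeks 6, 12 and 28) use "independent likelihood ratio tests using the treatment coefficient". The depression hypotheses 2.2a-d follow the same scheme, with the stratification covariates added and time points listed as weeks 0-6, 12 and 28.

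The article does not state ML or REML, a reference distribution, a degrees-of-freedom method or how intervals are formed.

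On numbers, Trial Status and Timeline reports that "A total of 49 participants were randomized to a study group", 26 to CBT-I and 23 to waitlist. It adds that "38 participants had completed the week 6 follow-up", "37 had completed the week 12 follow-up, 34 had completed the week 28 follow-up", and that there were "an additional 3 participants awaiting the 28-week follow-up".

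The only significance level appears under Power Calculation, where a two-group t test is used "at a 5% level of significance". The opening of Statistical Procedure and Data Analysis makes effect sizes and confidence intervals the main emphasis.

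**The concern.** A likelihood ratio test of fixed effects compares two models with different mean structures. It therefore needs maximum likelihood fits, because REML likelihoods are not comparable when the fixed effects differ. Maximum likelihood underestimates variance components in small samples, and the usual chi-square reference ignores the finite degrees of freedom left for estimating them. With 37 to 49 people both effects push the same way: p-values come out somewhat too small, and intervals from the same fit somewhat too short. The power calculation used a t test, which does allow for finite degrees of freedom; the analysis as described does not.

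At stake is the calibration of eight hypothesis tests and, more importantly for a feasibility trial, of the intervals meant to inform larger trials.

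**Working it through.** **Inputs.** From the article: 25 planned per group, d = 0.80, 5% level; 49 randomized (26/23); 38 and 37 seen at weeks 6 and 12; at week 28, 34 seen and 3 awaited, so at most 34 + 3 = 37. Assumed: two-sided tests, chi-square reference, and the variance components given below, since the article states none.

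**1. The plan's own figure.** Normal approximation: 0.80 × √(25/2) = 2.828; 2.828 − 1.960 = 0.868; Φ(0.868) = 80.7%. The exact noncentral t gives 79.1%. The stated 80% reproduces.

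**2. Exact benchmark for one coefficient.** In a normal linear model with n people and p mean parameters, the ML likelihood ratio statistic is n·ln(1 + t²/(n − p)). Setting it equal to 3.84 gives t² = (n − p)(e^(3.84/n) − 1).

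- n = 37, p = 2: t² = 35 × 0.1094 = 3.83, t = 1.957. On 35 df the true size is 5.8%.
- n = 49, p = 2: t² = 47 × 0.0816 = 3.83, t = 1.958. On 47 df the true size is 5.6%.
- With p = 4 the sizes are 6.6% (n = 37) and 6.2% (n = 49).

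**3. Intervals in the same benchmark.** With an unbiased variance and multiplier 1.960, coverage is 1 − 2·P(t > 1.960): 94.2% on 35 df and 94.4% on 47 df. With the ML standard error, the effective multiplier shrinks by √((n − p)/n). For n = 37 it is 1.960 × √(35/37) = 1.906, giving 93.5%; for n = 49 it is 1.960 × √(47/49) = 1.920, giving 93.9%.

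**4. Simulation of the planned insomnia model.** ML fits; weeks 0, 6, 12 and 28 as categories; AR(1) errors plus a random slope; no treatment effect; 4,000 trials per setting; Monte Carlo SE 0.34 points. Set A: residual variance 20, ρ = 0.5, slope variance 10. Set B: residual variance 20, ρ = 0.6, slope variance near 0. Dropout was completely at random. Rejection rates (%) at nominal 5%:

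| Setting | Set | Week 6 | Week 12 | Week 28 | Interaction, 3 df |
|---|---|---|---|---|---|
| 49 complete | A | 5.42 | 5.35 | 5.35 | 5.58 |
| 49 complete | B | 4.95 | 5.48 | 5.40 | 5.75 |
| 49, falling to 38/37/37 | A | 5.75 | 5.92 | 5.52 | 5.92 |
| 49, falling to 38/37/37 | B | 5.18 | 6.08 | 5.20 | 5.35 |
| 37 complete | A | 6.10 | 5.30 | 5.68 | 6.38 |
| 37 complete | B | 5.98 | 5.42 | 5.98 | 6.15 |

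The middle rows are closest to the planned intention-to-treat analysis: 5.2% to 6.1%.

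**5. Does the remedy work?** A further 2,000 null trials of the insomnia model, with 49 randomized and the same dropout, gave about 5.9-6.1% for the 1-df likelihood ratio test and about 4.6-4.9% for REML with a t reference on 35 df. The Monte Carlo SE is √(0.05 × 0.95/2000) = 0.49 points. Kenward-Roger itself was not simulated.

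**6. Depression model.** A run with nine visits, two covariates and complete data (4,000 trials, assumed ρ = 0.5, slope variance over 28 weeks half the residual variance) gave 6.2% for a 1-df test with 37 people and 5.6% with 49.

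**The case against.** The strongest reply is that the criticised rule is not in the article. It names the likelihood ratio test but not the chi-square reference, and such a test can also be calibrated by bootstrap, permutation or a Bartlett correction. A condensed article may leave this to a full protocol or analysis plan that is not shown. That stands, so chi-square is an assumption here, and its absence from the article is not itself the finding. What remains is that the test is named, that its ordinary meaning is ML with chi-square, and that Kenward-Roger or Satterthwaite t and F tests would replace the named test.

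The second reply is that the excess is about one point in a trial that puts estimation ahead of significance. That also stands, and it sets the weight of this point.

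Several stronger readings are tempting but unsupported:

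- *That every insomnia and depression hypothesis is affected.* Hypotheses 1.2a-b use logistic regression, 2.3 uses linear regression, and hypothesis 3 uses mixed models with no likelihood ratio test named.
- *That the error rate reaches about 7%.* One simulation gave 7.4% for a 16-df joint test of time and interaction in the nine-visit depression model with 37 complete cases; another gave 6.5%. Both treat time as categorical, which the article does not state, and drop the partial data that a mixed model keeps. Their null also requires no change over time in either arm, which is not the null of a between-group hypothesis. Further, the model names the BDI-II, which the Secondary Outcomes schedule does not place at weeks 1-6.
- *That a declared 5% level is broken.* That level is stated only for the power calculation.
- *That the article claims statistical independence of the three week-specific tests.* The word most naturally means separate, and no calculation relies on independence.

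**Conclusion.** The point holds as a minor improvement, limited to hypotheses 1.1a-d and 2.2a-d. If the likelihood ratio tests use ML fits and a chi-square reference, their actual size is about 5% to 6.5% at nominal 5%, and normal-based intervals from the same fit cover roughly 94%. The direction agrees between the exact benchmark and the simulations, although several individual simulated rates lie within Monte Carlo error of 5%. The size rests on assumed variance components, a correctly specified model and, where dropout was simulated, dropout completely at random. Interval coverage comes from the benchmark, not from simulating the mixed model. The trial's conclusions are unlikely to change.

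**What to change.** Replace the likelihood ratio wording for 1.1a-d and 2.2a-d with one sentence: the mixed models are fitted by REML, and tests and 95% confidence intervals use t references (single contrasts) or F references (joint tests) with Kenward-Roger or Satterthwaite degrees of freedom.

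The cost is that sentence, a standard software option and slightly wider intervals. In the benchmark the multiplier rises from 1.960 to 2.030 on 35 df (2.030/1.960 = 1.036, or 3.6%) and to 2.012 on 47 df (2.6%). Moving from ML to REML standard errors adds √(37/35) = 1.028, or 2.8%, at n = 37.

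The article says that week 6 interim analyses had been run but that the primary hypotheses had not been tested in full. The change should therefore be dated and applied to all eight hypotheses alike.

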##### Well-being

We measure change in depressive symptoms as primary outcomes of well-being. Depressive symptoms are evaluated using the Patient Health Questionnaire-9 (PHQ-9) [48]. The PHQ-9 is a self-administered, 9-item questionnaire that assesses each of the 9 DSM-IV depression criteria. The total score ranges from 1 to 27. Answers are given on a 4-point Likert scale ranging from 0 (Not at all) to 3 (Nearly every day), with higher scores reflecting increased severity of depressive symptoms.

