#### Secondary Outcomes

All secondary outcomes of insomnia and well-being are collected at weeks 0, 12, 28, and 56. Secondary measures of insomnia and the Generalized Anxiety Disorder-7 (GAD-7) are also collected at weeks 1-6.

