The Beck Depression Inventory-II (BDI-II) [59,60] is used as a secondary measure of depressive symptom change over time. We will sum all items except one sleep item, and the average item score for the remaining 20 items will be multiplied by 21 (the original number of items) to create a modified depression scale that maintains the original range (ranges: 0-13, minimal; 14-19, mild; 20-28, moderate; and 29-63, severe). The BDI-II is a 21-item self-report scale with high validity and reliability that assesses the severity of depressive symptoms. The depressive items consist of sadness, pessimism, past failure, loss of pleasure, guilty feelings, punishment feelings, self-dislike, self-criticalness, suicidal thoughts or wishes, crying, agitation, loss of interest, indecision, worthlessness, loss of energy, changes in sleep pattern, irritability, changes in appetite, concentration difficulty, tiredness or fatigue, and loss of interest in sex. Items are scored from 0 to 3, and higher scores indicate greater level of severity.

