Hypotheses 1.2a and 1.2b are that individuals who were assigned to the CBT-I group will be less likely to have an insomnia diagnosis than those who were assigned to the waitlist control group at weeks 12 and 28. These hypotheses will be tested using 2 separate logistic regression models, one using the short-term (hypothesis 1.2a; 12 weeks) and one using long-term (hypothesis 1.2b; 28 weeks) follow-up insomnia diagnosis, as defined by the Duke, as the dependent variable, with treatment (CBT-I, waitlist) as the independent variable.

Statistical analyses aim 2 is to determine whether a brief, telehealth CBT-I improves well-being during the COVID-19 pandemic. We will test whether immediate CBT-I is superior to a waitlist control in improving depressive symptoms as the primary measure of well-being during the waitlist-controlled period (28-week duration) by using a mixed effects linear model with autoregressive error structure using intention-to-treat analysis. Depression severity, as assessed by the BDI-II, will be entered as the dependent variable with baseline covariates used for stratified randomization (ie, baseline insomnia severity and sex), group (immediate CBT-I or waitlist control), time point (weeks 0-6, 12, and 28), and group-by-time interaction included as fixed effects. The model will also include a random slope. Separate, secondary analyses will be conducted on the secondary measures relating to well-being described in the Secondary Outcomes section (eg, anxiety, suicidality, quality of life). Several hypotheses will be tested using this model.

Hypothesis 2.2a is that individuals assigned to the CBT-I group will have an improved trajectory of depressive symptoms across the 28 weeks relative to individuals assigned to the waitlist control group. This hypothesis will be tested using a likelihood ratio test of the coefficients of the time and group-by-time interaction terms of the aforementioned mixed effects linear model.

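### The primary depression model uses the BDI-II, which the protocol declares secondary and does not schedule at weeks 1 to 6, while the declared primary depression measure is the PHQ-9

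*Protocol article*

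**What the plan says.** Two parts of the protocol article define the depression outcome.

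- **Primary Outcomes, Well-being.** "We measure change in depressive symptoms as primary outcomes of well-being", and the instrument follows at once: "Depressive symptoms are evaluated using the Patient Health Questionnaire-9 (PHQ-9". The opening paragraph of Primary Outcomes has the primary well-being measure collected at weeks 0, 6, 12, 28 and 56, and also at weeks 1 to 5.
- **Secondary Outcomes.** In the Well-being part, the BDI-II "is used as a secondary measure of depressive symptom change over time". On timing: "All secondary outcomes of insomnia and well-being are collected at weeks 0, 12, 28, and 56". The only additions at weeks 1 to 6 are the secondary insomnia measures and the GAD-7.

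Two parts of Primary Analyses then use the outcome.

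- **Aim 2 mixed model.** The stated purpose is to test superiority in "improving depressive symptoms as the primary measure of well-being during the waitlist-controlled period (28-week duration"), yet "Depression severity, as assessed by the BDI-II, will be entered as the dependent variable", with "time point (weeks 0-6, 12, and 28), and group-by-time interaction included as fixed effects". Hypotheses 2.2a to 2.2d are all tested in this model, and 2.2b is the contrast at week 6.
- **Mediation analysis (hypothesis 2.3).** Depressive symptoms are again called the primary outcome measure, but the instrument named is the PHQ-9.

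Trial Status and Timeline adds that, at the time of writing, "we had conducted interim analyses for the week 6 follow-up", while the primary hypotheses had not been tested in full.

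**The concern.** The sentence that defines the primary aim 2 model names an instrument that the outcome section ranks as secondary. It also pairs that instrument with weekly time points at which the protocol does not schedule it. An analyst who follows the text cannot produce a week-6 depression contrast from week-6 data, although week 6 is one of the three declared primary time points. An analyst who substitutes the PHQ-9 departs from the written model.

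The choice of scale is not neutral. The BDI-II score is built without one sleep item and rescaled to its full range. No comparable adjustment is described for the PHQ-9. In a trial of a sleep treatment, the two scores could give different depression effects. A feasibility trial that will report effect sizes with intervals needs one defined outcome for each effect size.

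**Working it through.** **The plan's own figure.** Power Calculation gives 80% power with 25 per group for d = 0.80 at a 5% level. By the two-sided normal approximation, power = Φ(d·√(n/2) − 1.96) = Φ(0.80 × √12.5 − 1.96) = Φ(0.87), about 80.7%. The noncentral t gives 79.1%. The figure reproduces. It is a standardised difference at week 28 and names no instrument, so this point does not affect it.

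**Time points against collection schedule.**

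| Week in the aim 2 model | BDI-II scheduled (Secondary Outcomes) | PHQ-9 scheduled (Primary Outcomes) |
|---|---|---|
| 0 | yes | yes |
| 1, 2, 3, 4, 5 | no | yes |
| 6 | no | yes |
| 12 | yes | yes |
| 28 | yes | yes |

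- Model time points: 7 (weeks 0 to 6) + 2 (weeks 12 and 28) = 9.
- With the BDI-II: 3 of 9 have scheduled observations (weeks 0, 12, 28), and 9 − 3 = 6 have none (weeks 1 to 6).
- With the PHQ-9: 9 of 9 have scheduled observations.

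**Consequence for each hypothesis if the BDI-II is used.**

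- 2.2a (trajectory to week 28): can be tested, but on 3 occasions instead of 9, with nothing during treatment or just after it.
- 2.2b (week 6): no scheduled observation in either arm. With time as a factor there is no week-6 coefficient to estimate. With time continuous, a week-6 difference can be computed, but only as an interpolation between weeks 0 and 12.
- 2.2c and 2.2d (weeks 12 and 28): can be estimated, on a measure declared secondary.

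So 1 of the 3 week-specific contrasts has no data of its own.

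**Which instrument the rest of the text supports.** The outcome designation, the weekly collection of the primary well-being measure and the mediation analysis all point to the PHQ-9. Only the instrument name in the aim 2 model points to the BDI-II, and that model's own list of weeks matches the PHQ-9 schedule.

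**The case against.** The strongest reply is that this is a drafting slip. No section labels the BDI-II primary, and everything around the one sentence fits the PHQ-9. That is probably right, but the protocol does not say so. The slip sits in the sentence that carries all four aim 2 depression hypotheses, so it still has to be corrected.

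A second reply is that the BDI-II may have been collected weekly after all. The Abstract and Overall Design mention assessment of well-being or depressive symptom severity at weeks 1 to 6. Neither names an instrument, and the PHQ-9 satisfies both. The schedule sentence is itself a little loose: it puts the secondary insomnia measures at weeks 1 to 6, whereas the sleep diaries are described at weeks 1 to 5. The absence of weekly BDI-II data is therefore what the schedule states, not an established fact about the database.

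A third reply is that continuous time would rescue the week-6 contrast. The section does not say that time is categorical, and it includes a random slope, so it would be too strong to call the contrast impossible to compute. What stands is that it would contain no week-6 observation.

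A fourth is that the trial is a feasibility study that puts effect sizes ahead of significance. That lowers the confirmatory stakes but does not settle which outcome the effect size belongs to.

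A reader might go further and infer that the investigators had seen unblinded week-6 results and could pick the better of two scales. The documents do not support this. Trial Status and Timeline does not say which outcomes were analysed, whether by arm, or who saw the results. If the BDI-II was not collected at week 6, that look could not have compared the two scales. The remaining risk is narrower: if PHQ-9 results at week 6 were examined by arm, they could influence which instrument is used at weeks 12 and 28.

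**Conclusion.** The contradiction holds. The primary aim 2 model names a measure declared secondary. By the stated schedule, 6 of its 9 time points, including week 6, have no scheduled BDI-II observations. Hypothesis 2.2b cannot be estimated from observed week-6 data, 2.2a loses its weekly part, and 2.2c and 2.2d would rest on the secondary measure. The PHQ-9 covers every time point.

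This assumes that the schedule under Secondary Outcomes applies to the BDI-II as written. It does not depend on how time is coded, except that continuous time would give an interpolated week-6 value instead of none. It makes no claim that the outcome was chosen on results. The correction should be made before the full primary analysis, because a primary hypothesis cannot be carried out on week-6 data as the text stands.

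**What to change.** - In Primary Analyses, aim 2, name the PHQ-9 as the dependent variable of the primary model at weeks 0 to 6, 12 and 28. This agrees with Primary Outcomes and the mediation analysis. The authors should confirm that it is what they intended.
- Run the BDI-II model as a secondary analysis at weeks 0, 12 and 28 only.
- Report when the primary instrument was fixed relative to the week-6 interim analyses, and which outcomes those analyses covered. The authors should state what happened; the documents do not establish the order of events.

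The cost is wording. No new assessments are needed, although follow-up was not complete at the time of writing: 3 participants awaited week 28 and 23 awaited week 56. There is one small downside. Because a sleep item is dropped from the BDI-II score and no such step is described for the PHQ-9, the PHQ-9 result may overlap more with sleep. The secondary BDI-II analysis at weeks 12 and 28 serves as a check on that.

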Hypotheses 2.2b-2.2d are that individuals assigned to the CBT-I group will have lower depressive symptoms compared who those who were assigned to the waitlist control group immediately posttreatment (hypothesis 2.2b; week 6) and at the short-term (hypothesis 2.2c; week 12) and long-term (hypothesis 2.2d; week 28) follow-ups. These hypotheses will be tested using the aforementioned mixed effects linear model with independent likelihood ratio tests using the treatment coefficient for the posttreatment (hypothesis 1.2b; week 6), short-term (hypothesis 1.2c; week 12), and long-term (hypothesis 1.2c; week 28) follow-up time points.

Hypothesis 2.3 is that improvement in insomnia symptom severity (measured by the ISI) will mediate subsequent improvement in well-being from baseline (week 0) to posttreatment (week 6), short-term follow-up (week 12), and long-term follow-up (week 28). Using the approach described by Kraemer at al [61] and Manber et al [34], linear regression analyses will be used to determine whether change in the ISI score from Session 1 (week 1) to Session 4 (week 5) of treatment mediates the subsequent depressive symptom improvement (primary outcome measure) after the completion of treatment (week 6). Change in ISI score at Session 4 will be estimated as the slope of the regression line of ISI scores from Session 1 (week 1) through the treatment phase to Session 4 (week 6) using all available data from each participant. The model will include group (CBT-I or waitlist control), change in ISI score from Session 1 to Session 4 (participant specific slopes), and their interaction with depression severity, as measured by the PHQ-9, as the dependent variables. Mediation will be tested using the MacArthur approach as described by Kraemer et al [62]. Specifically, a mediation effect requires a significant effect of the intervention on the mediator (Path A in Figure 3) and a significant association between the mediator and the outcome (Path B in Figure 3).

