#### Secondary Analyses

Secondary analyses will be conducted. (1) Analytic methods described in the primary aims will be repeated but applied to secondary measures of sleep disturbance and well-being outcomes as described in the Secondary Outcomes section. (2) Analytic methods described in the primary aims will be repeated but applied to outcome measures collected at week 56. (3) Sparse unsupervised clustering and principal component analysis analyses will be used to identify cohesive factors of dysfunction in sleep complaints and patterns of mental health outcomes at baseline. Regression models will be used to quantify the relationships within and between sleep complaints and patterns of mental health outcomes. (4) Age and sex differences in treatment response and as moderators of relationships between sleep complaints, insomnia risk factors, and mental health outcomes will be explored.

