This study was conceived and launched in response to the global pandemic of COVID-19, which, while rendering it novel, presents unique challenges. First, to address our scientific questions, we sought to recruit participants early in the course of their sleep disturbance, causing a significant urgency to launch the study. This time pressure led us to conduct this study with limited resources, which impacted our recruitment efforts. We were unable to offer compensation for participation. We relied heavily on recruiting participants through free online platforms, such as social media posts, online message boards, and electronic newsletters. Due to these recruitment concerns and the resulting decreased statistical power for the planned analysis, we view this as a feasibility study. Therefore, the planned analyses and publications resulting from this protocol will utilize effect size estimates, rather than statistical significance, to provide pilot and feasibility data to inform future hypotheses. A second potential limitation is the unequal attrition rate in the treatment versus the waitlist control group. Since participants are not financially compensated, the primary motivation of participation is meeting with a therapist on a weekly basis to address their sleep concerns. Thus, it is possible that individuals in the waitlist control group were more likely to decline to participate in follow-up time points due to loss of interest or spontaneous improvement in symptoms over time. Although this could potentially affect the ability to detect significant differences in between-group comparisons at the long-term follow-up time points due to inadequate power, our analytic approach using regression models has the advantage of increased efficiency and power over unadjusted analyses [63,64]. We will address this issue by assessing whether missingness is related to any observed covariates. If this is the case, an issue of greater concern is the potential bias in the estimate of the treatment effect if neither the missing completely at random (MCAR) nor the missing at random (MAR) assumption holds. Although mixed effects linear models lead to unbiased estimates of the treatment effect under the MCAR and MAR assumptions, estimates may be biased under nonignorable missingness. Further sensitivity analyses will be performed if this is the case.

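### The aim 2 depression model does not adjust for baseline depression, so the week 6, 12 and 28 contrasts are valid but less precise than the collected data allow

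*Protocol article*

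**What the plan says.** The Primary Analyses section (aim 2) specifies a mixed effects linear model with autoregressive errors and a random slope. The dependent variable is the BDI-II. The fixed effects are baseline insomnia severity and sex (the stratification factors), group, "time point (weeks 0-6, 12, and 28), and group-by-time interaction included as fixed effects". No baseline depression term is listed, and nothing sets the group difference at week 0 to zero.

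Hypotheses 2.2b to 2.2d are then tested with "independent likelihood ratio tests using the treatment coefficient for the posttreatment (hypothesis 1.2b; week 6") and the matching coefficients for weeks 12 and 28. (The labels in that sentence read 1.2b and 1.2c, but the context is 2.2b to 2.2d.) The text does not say whether this coefficient is the group difference at the visit or the group difference in change from week 0.

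The Discussion answers a worry about inadequate power at long-term follow-up by saying that "our analytic approach using regression models has the advantage of increased efficiency and power over unadjusted analyses". The Secondary Analyses section extends the model to other scales: "Analytic methods described in the primary aims will be repeated but applied to secondary measures of sleep disturbance and well-being outcomes".

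The Power Calculation section uses an unadjusted two-group t test "based on the difference between CBT-I and waitlist control group at 28 weeks, at a 5% level of significance". It names no outcome.

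**The concern.** Depression is measured at week 0 and was not a stratification factor, so randomisation leaves its balance to chance. In a model with week 0 as a free outcome level, complete data and categorical time, the coefficient at a visit is the raw difference in means, or the raw difference in change, apart from the listed covariates. Neither uses the baseline score efficiently.

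The listed covariates may add little. The Randomization section stratifies insomnia severity as ISI 10 or more versus below 10, but eligibility requires a current ISI of 10 or more. Used as stratified, that factor is constant and only sex remains.

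The article places its main emphasis on effect sizes and confidence intervals, and 49 people were randomised. At stake is the width of those intervals, and how far each estimate moves with a chance difference in entry depression.

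**Working it through.** **Inputs from the article.** 25 per group, d = 0.80, 5% level (Power Calculation); "26 to the CBT-I group and 23 to the waitlist control group" and "34 had completed the week 28 follow-up", with 3 more awaited, so at most 37 (Trial Status and Timeline).

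**Assumptions.** Two-sided test; r not given, taken as 0.3 to 0.7; d = 0.80 applied to depression; a 19/18 split of the 37, since no split by arm is given.

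**Step 1: the plan's own figure.** The article states "With 25 per group, the study is 80% powered to detect a large effect size (Cohen d=0.80"). The variance of the difference is 1/25 + 1/25 = 0.080, so SE = 0.283 SD. Power is 80.7% by the normal approximation and 79.1% by the noncentral t with 48 df. The stated 80% reproduces. One-sided power would be 88.2%, which does not fit.

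**Step 2: variance factors** (complete data, categorical time, r between week 0 and the visit):
- difference at the visit: 1
- difference in change from week 0: 2(1 − r)
- baseline-adjusted, or common week 0 mean: 1 − r²

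The third is never larger than either of the others. At r = 0.5 the factors are 1, 1 and 0.75. The variance falls from 0.080 to 0.060 and the SE from 0.283 to 0.245, a ratio of 0.866, or about 13% narrower.

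**Step 3: power at 25 per arm, d = 0.80, noncentral t.**

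| r | visit difference | change | adjusted | forgone vs visit | forgone vs change |
|---|---|---|---|---|---|
| 0.3 | 79.1% | 64.9% | 82.7% | 3.6 | 17.8 |
| 0.4 | 79.1% | 71.6% | 85.6% | 6.5 | 14.0 |
| 0.5 | 79.1% | 79.1% | 89.2% | 10.1 | 10.1 |
| 0.6 | 79.1% | 87.3% | 93.4% | 14.2 | 6.1 |
| 0.7 | 79.1% | 94.7% | 97.2% | 18.1 | 2.5 |

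The two readings of the coefficient agree only at r = 0.5.

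**Step 4: week 28 with dropout, r = 0.5.** The planned model keeps the week 0 scores of those who drop out. The free-baseline variance is therefore (0.75/19 + 0.25/26) + (0.75/18 + 0.25/23) = 0.1016, and power is about 68%. With adjustment it is 0.75 × (1/19 + 1/18) = 0.0811, and power is about 78%. A completers-only t test (variance 0.1082, about 66%) is not the planned analysis and is the wrong comparator.

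**Step 5: chance imbalance.** With 26 and 23 per arm, the SD of the baseline difference D is √(1/26 + 1/23) = 0.286 SD units, and P(|D| > 0.3) is about 29%. Given D, the visit contrast shifts by r·D and the change contrast by −(1 − r)·D. At r = 0.5 each shifts by half of D.

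**Step 6: sensitivity to the planned structure.**
- Autoregressive errors: if lag-one correlation is 0.9 (assumed) and the random slope is ignored, r between weeks 0 and 28 is 0.9^28 = 0.05 when lag is counted in weeks, or 0.9^8 = 0.43 when counted by visit order. The gain over the visit difference is then 0.1 or 7.5 points. Over the change contrast a low r works the other way, as Step 3 shows.
- Linear time at r = 0.5 (normal approximation): 83.1% against 90.7% for the visit difference with visits 0, 12 and 28; 94.0% against 95.3% for the change contrast with visits 0 to 6, 12 and 28.

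**The case against.** The strongest reply is that this is a standard and valid repeated-measures model, and that the article puts estimation ahead of testing in a feasibility trial. That stands. A reader might infer that the contrasts are biased, but randomisation keeps them unbiased on average. The cost is variance, plus a shift conditional on the imbalance that happened to occur.

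A reader might also infer that the trial loses 10 points from its stated 80%. The article does not support that. Its 80% is for an unadjusted t test on an unnamed outcome and is retained; what is missing is a gain. The 10 points also need r = 0.5, which the article does not give.

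Nor does a uniform 25% cut in variance at weeks 6, 12 and 28 follow. That figure needs a constant correlation of 0.5, whereas the plan has autoregressive errors and names no random intercept.

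Finally, it would go too far to call the efficiency statement in the Discussion wholly wrong. The mixed model recovers some information from dropouts, as Step 4 shows, and sex is adjusted for. For depression, though, the listed terms do not secure the efficiency that the statement relies on.

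There is also a more basic difficulty. The Secondary Outcomes section schedules the BDI-II at weeks 0, 12, 28 and 56 only, while the Primary Outcomes section names the PHQ-9 as the depression measure and has well-being collected at weeks 0 to 6 as well. A week 6 contrast on the BDI-II therefore has no scheduled data behind it. This limits where the point applies but does not remove it, since either scale has a week 0 score.

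**Conclusion.** The point holds as a forgone gain in precision, not as an error of validity. At r = 0.5 and 25 per arm the intervals could be about 13% narrower, equal to about 10 points of power at d = 0.80 if that effect is applied to depression. For r from 0.3 to 0.7 the range is about 4 to 18 points against the visit difference and about 18 to 2.5 points against the change contrast; the article leaves open which of the two is meant. At week 28 with 19/18 assumed, and r = 0.5, power moves from about 68% to about 78%. The gain over the visit difference shrinks if the correlation decays by week 28, and the gain is smaller in the linear-time cases checked. With so few participants and the baseline scores already in hand, the change should be made.

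**What to change.** First reconcile the BDI-II named in the aim 2 model with the PHQ-9 named under Primary Outcomes, and list only the visits at which the chosen scale is collected. Then use one of two forms:

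- Keep week 0 in the outcome and constrain the arms to a common week 0 mean: drop the group main effect and keep group-by-time at the post-baseline visits.
- Take week 0 out of the outcome and enter the continuous week 0 depression score and its interaction with time as covariates. This form estimates the baseline relation at each visit from the data and leans less on the assumed error structure.

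Base hypotheses 2.2b to 2.2d on the adjusted differences at the collected visits, and say that these are the contrasts meant. Use the same form, with each scale's own week 0 score, for the secondary well-being measures. Keep the published model as a sensitivity analysis.

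The cost is wording, plus the covariate degrees of freedom or an assumption of equal week 0 means that randomisation justifies. No new data are needed. Because the article reports that interim week 6 analyses had been run while the primary hypotheses had not been tested in full, record and date the change before the full analysis.
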